## Abstract

**Background:**

Considering the insufficiently controlled spread of new SARS-CoV-2 variants, partially low vaccination rates, and increased risk of a post-COVID syndrome, well-functioning, targeted intervention measures at local and national levels are urgently needed to contain the SARS-CoV-2 pandemic. Surveillance concepts (cross-sectional, cohorts, clusters) need to be carefully selected to monitor and assess incidence and prevalence at the population level. A critical methodological gap for identifying specific risks/dynamics for SARS-Cov-2 transmission and post-COVID-19-syndrome includes repetitive testing for past or present infection of a defined cohort with simultaneous assessment of symptoms, behavior, risk, and protective factors, as well as quality of life.

**Methods:**

The ELISA-Study is a longitudinal, prospective surveillance study with a cohort approach launched in Luebeck in April 2020. The first part comprised regular PCR testing, antibody measurements, and a recurrent App-based questionnaire for a population-based cohort of 3000 inhabitants of Luebeck. The follow-up study protocol includes self-testing for antibodies and PCR testing for a subset of the participants, focusing on studying immunity after vaccination and/or infection and post-COVID-19 symptoms.

**Discussion:**

The ELISA cohort and our follow-up study protocol will enable us to study the effects of a sharp increase of SARS-CoV-2 infections on seroprevalence of Anti-SARS-CoV-2 antibodies, post-COVID-19-symptoms, and possible medical, occupational, and behavioral risk factors. We will be able to monitor the pandemic continuously and discover potential sequelae of an infection long-term. Further examinations can be readily set up on an ad-hoc basis in the future. Our study protocol can be adapted to other regions and settings and is transferable to other infectious diseases.

**Trial registration:**

DRKS.de, German Clinical Trials Register (DRKS), Identifier: DRKS00023418, Registered on 28 October 2020.

**Supplementary Information:**

The online version contains supplementary material available at 10.1186/s12889-022-13666-z.

## Background

From initial local reports from China on infections with SARS-CoV-2 in December 2019, the disease rapidly evolved from an epidemic to a pandemic, with over 270 million confirmed cases and 5 million COVID-19 patients deceased worldwide [1]. The emergence of the new SARS-CoV-2 variant B.1.617.2 (Delta) in December 2020 and especially variant B.1.1.529 (Omicron) in November 2021^2^ led to vastly increased infection rates, including a significant number of vaccination breakthroughs [2]. While currently available vaccines against SARS-CoV-2 reduce the frequencies of severe cases and hospitalization rates with mostly mild cases in fully vaccinated patients, the impact of highly contagious variants such as B.1.1.529 (Omicron) is concerning because vaccination only has a limited effect on spread and development of COVID-19 [3, 4]. Thus, the emergence of new variants such as B.1.1.529 (Omicron) can quickly transform previous low-incidence areas into hotspots. In the municipal area of Luebeck in Northern Germany, where the current study protocol was initiated, the 7-day incidence rate rose from 20 infections per 100,000 inhabitants in October 2021 to 1190 infections per 100,000 inhabitants in February 2022 [5].

Considering the insufficiently controlled spread of new SARS-CoV-2 variants, low vaccination rates, and increased risk of post-COVID syndrome, well-functioning, targeted intervention measures at local and national levels are urgently needed to control the spread of SARS-CoV-2. Surveillance strategies should be as adaptable as possible to consider regional conditions and different spread scenarios. Surveillance concepts (cross-sectional, cohorts, clusters) need to be carefully chosen to monitor and assess incidence and prevalence at the population level to contain the massive spread of infections. Longitudinal studies in defined, population-based cohorts at the population level are currently scarce, often cross-sectional, and usually cover only relatively short time intervals [6]. Likewise, recently conducted antibody prevalence studies were conducted cross-sectionally. They covered only short periods in specific regions, such as different parts of Germany [7–12], Great Britain [13], northeastern Italy [14], California [15], Pakistan [16], Portugal, [17] and Peru [18].

A critical methodological gap for identifying specific risks/dynamics for transmission and post-COVID-19-syndrome includes repetitive testing of a defined cohort with simultaneous assessment of symptoms, behavior, risk, and protective factors, as well as quality of life. Therefore, a longitudinal, prospective surveillance study with a cohort approach was started in Luebeck in April 2020. The study was performed on people living in the City of Luebeck/Germany (approx. 220,000 inhabitants, population density approx. 1000/sqm). In the first part of the study, more than 3000 people, corresponding to approximately 1% of the catchment area in and around Luebeck, were examined in person at regular intervals. The results of this part of the study were recently published [19].

Methodological details on study design and protocol have not been previously reported and are presented here as an easily adaptable template for further studies, particularly in other regions. Furthermore, we present the protocol of a follow-up study, which will investigate the cohort after the sharp increase of cases in March 2022 due to the new SARS-CoV-2 B.1.1.529 (Omicron) variant [20]. Key focus of this follow-up study will be studying immunity after vaccination and/or infection, as well as post-COVID-19-symptoms in our defined cohort. For this, we have adapted our methods so that a study test center is no longer necessary and that participation can now be easily conducted from home.

In the following, we describe the study protocol and provide an easily transferable model for effective surveillance that allows for monitoring incidence prevalence, as well as re-infection rates, and enhancing preparedness for future potential pandemics. The study is funded by the National Research Network of University Medicine on COVID-19 in surveillance and testing (B-Fast work package 4), the Federal State of Schleswig-Holstein, and a crowdfunding campaign of the University of Luebeck.

## Methods

### Study aims

To monitor the prevalence and incidence of SARS-CoV-2 in the general population of the Luebeck municipal areaTo estimate the extent of undetected SARS-CoV-2 infections in the general population of the Luebeck municipal areaTo assess the influence of hygiene measures (e.g., mandatory mask-wearing) over time and in response to the implementation and release of official lockdown and containment measures.To identify behavioral and occupational factors (e.g., occupation, working from home, using public transportation, meeting with others) that may increase the risk of infection and post-COVID-19-syndrome.

### Study centers

Design and implementation of a local test center that meets pandemic hygiene regulations to perform recurrent nasopharyngeal swabs and blood collection for antibody testing in a cohort representative of the general population.Design and implementation of a data center to collect, assemble, and analyze pseudonymized study data from different sources (app, test center, diagnostic laboratories).

### IT infrastructure

Study App (Perfood GmbH, Lübeck)◦ Cell-phone app for paperless, repeated application of questionnaires for the collection of standardized behavioral data◦ Questionnaire for follow-up testingOnline Booking (www.timify.com), (Timify, München)◦ Booking timeslots for test center visitsSubject database (In-house, web-based, MySQL, and PHP)◦ Contactless check-in at the test center◦ Documentation of test center visits◦ Pseudonymized sample assignmentSample database (In-house, web-based, MySQL, and PHP)◦ Tracking biological material at different locations (i.e., test center, diagnostic laboratories, biobank, data center)◦ Biobanking

### Setting

With approximately 220,000 inhabitants, the Luebeck area is part of the greater Hamburg metropolitan region and a major tourist destination in Germany. Around 7000 people commute between Luebeck and Hamburg, and an average of 50,000 tourists visit Luebeck per day [21].

### Study design

The study is designed as a prospective, longitudinal, surveillance cohort study, involving seven rounds of in-person testing with a representative and a risk-based sample of citizens of the Luebeck metropolitan area (total *n* = 3000) in a first part [19]. The second part involves a mostly self-reported follow-up on re-infections and current health status. The ethics committee approved both parts of the study protocol of the University of Luebeck. Study details were submitted to the German Clinical Trial Register (DRKS) (Identifier: DRKS00023418).

### Study procedures

#### Recruitment and sample

Initial cohort recruitment took place in April 2020 via local press and radio announcements, posters, flyers, an announcement by the mayor of Luebeck on the city’s official homepage, as well as University internal e-mail distribution. Inclusion criteria comprised residence in the metropolitan area of Luebeck, age 18 years or older, active consent for study participation, registration for study participation via the study app, and willingness and ability to come to the local study test center for regular PCR testing and antibody measurements. Study registration and consent were app-based, using an existing cell phone app (MillionFriends, Perfood GmbH) established by a start-up company that emerged from the University of Luebeck (see below).

Activation of the study app marked the start of the study and, based on the information provided in the initial questionnaire (e.g., age, occupation, gender), a sample representative of the Luebeck population (*n* = 2145) was drawn from 7303 registered individuals, as well as a risk group consisting of individuals with a high number of professional contacts with other people (*n* = 1374). Ultimately, 3474 individuals were selected and invited via an e-mailed link to make the first appointment at the study test center using an online appointment booking app.

#### App

An existing collaboration with Perfood GmbH (perfood.de) was utilized, and the study questionnaires were integrated into their existing app. No personal data other than an email address had to be entered in the app to participate in the study. A unique hash was generated by the app for each individual participant and used to link the app data to the study data in the data center. The QR-code of this hash was used for contact-less check-in at the study center. An initial questionnaire was started when logging into the app; after that, a follow-up questionnaire was activated every 3 days. Data was collected on the app data server and was accessible by the study’s data center.

#### Test center and initial testing procedure

In collaboration with the local health authorities, we established the test center at a local conference center (Media Docks Luebeck, https://www.mediadocks.de/), which was identified as a suitable study center due to various characteristics: (i) The central location in Luebeck’s city center and availability of parking, (ii) its layout with a total of six rooms that were 25–50 m^2^ in size that could all be accessed from the outside, thereby providing maximum safety at times of a pandemic; (iii) sufficient storage space and office space for administrative activities. Participants were invited by the study data center per email using the email address entered into the study app. The invitation also included links to the study homepage (https://elisa-luebeck.de), where participants could find the study information, consent documents, and a video explaining the examination procedure. Subjects were asked to make their bookings in advance using the online tool Timify (https://web.timify.com/), which limited appointments to five per 15 minutes to prevent clustering of subjects at the study center at any time. A call center gave support to participants each workday from 8 to 12 am. The check-in room was set up with two separate counters facing outwards. Subjects were able to check in using their personal QR code from the study app and a barcode-scanner linked to the subject database.

At the first study visit, information about the study, written informed consent for participation, and answers to any questions were provided by the medical staff at this counter. After consenting to the study, personal data (name, address, telephone number) were recorded in the subject database of the test center (Table 1). Uniquely generated 8-digit barcodes were placed on all collected biological materials allowing the unambiguous assignment of the samples to the respective study subject by the study data center but not the diagnostic laboratories. This barcode was also stored as the identifier for the sample database of the biobank. By having the participants take their own barcoded specimen tubes into their study rooms themselves, the risk of specimen mix-up was minimized. Subjects were assigned to a specific study room, where specially trained medical students or staff performed the swab and blood sample collection. After sample collection, participants exited the building directly from the study room. The first appointment took approximately 15 min per person, including check-in, obtaining informed consent, personal data collection, and sample collection. Subsequent appointments usually took less than 10 min, including just the check-in and sample collection.

**Table 1 Tab1:** Collected proband data

Personal data	Questionnaire topics	Laboratory data
Name	Covid Symptoms	**In person visits**
Address	Daily activities	Nasopharyngeal swab for PCR for SARS-CoV-2
Email	Recent travel	EDTA blood for DNA analyses
Telephone number	Adherence to lockdown measures	Serum for antibody analyses
Sex	Allergies	**Follow-up**
Age	Medication and supplements	Dried blood spot for antibody analyses
Education	Medical history	Nasopharyngeal swab for PCR testing of respiratory viruses
Occupation	Smoking	
Weight	Alcohol consumption	
Height	Pets	
	Well – being	
	Vaccination status	

Once samples were collected, they were immediately stored at 4 °C until courier pick up at the latest at 8 am the following day.

The study center was operated in a two-shift system, where shifts overlapped for 30 minutes mid-day to avoid interruptions concerning sample collection. Shifts always started 30 minutes before the center opened to prepare check-in and study rooms. Depending on the utilization of the test center facilities, which could be estimated in advance based on the status of the online bookings, 4–6 medical students were assigned to each shift. Their main task was to collect samples, but they also provided organizational support, e.g., check-in of the test persons and sample management. A physician was always present at the study site to provide overall supervision of the study site, supervise blood and swab collection, and answer questions from both student personnel and participants at all times. During the initial visit phase, up to three physicians were simultaneously present at the study center. Testing was conducted from Monday to Friday from 8 am to 6 pm, and 9 am to 1 pm on Saturdays. On average, around 180 participants visited the study center per day, with a maximum of 230 and a minimum of about 50 participants.

Testing of the study cohort took place over 12 weeks from May to July 2020 at three-week intervals and in August 2020, November 2020, and February 2021 (Fig. 1). This period included important pandemic-related milestones, such as the end of the first lockdown, the summer holiday season with a high influx of tourists, the steep increase in infection rates in the fall/winter of 2020/2021, and the second lockdown.

**Fig. 1 Fig1:**
[figure not shown]
Timeline of the ELISA Study

For the second part of the study, participants will be invited via mail or email for follow-up testing on time point 8 and provided with a modified online questionnaire and instructions and material to prepare dried blood spots (DBS). These will be mailed back to the study center in a prepared envelope, where laboratory and statistical analyses will be conducted (s. below). In addition, we will ask 500 subjects to return to the study center to be tested via PCR regarding other respiratory viruses (s. below).

#### Reporting of findings

In case of positive PCR results, patients were immediately contacted by an assigned study physician, usually within 48 hours of sample acquisition, and local Health Authorities were notified. Depending on current regulations, patients were then quarantined between 10 and 14 days. Negative test results were sent to the participant within approximately 7 days by email in the study’s first phase. Antibody results were initially reported to the study participants by the study staff at the test center. Later, a personalized study portal was implemented, summarizing all study visits, including PCR and antibody tests results.

In the second phase of the study, participants without detectable SARS-CoV-2 antibodies will be informed after analysis of the data.

#### Personnel

The study involved a leadership team comprising seven specialists on clinical study design, epidemiology, diagnostics of infectious diseases, virology, immunology, software & database development, and ethics. A team of three full-time clinician-scientists was involved in the design, logistics, setting up of the test center, as well as training and supervision of the medical students. The test center was supported by 30 medical students and one secretary for the call center. PCR diagnostic teams were located at the University Hospital Schleswig Holstein (UKSH) and the Research Center Borstel. They involved a supervising diagnostician, as well as a team of at least two technicians or specifically trained life-science students on each location. PCR diagnostics were further supported by external diagnostic laboratories, including the LADR laboratory in Geesthacht (Hamburg) and Centogene (Rostock). The study further involved one computer scientist for data handling, study portal, and the online questionnaire and a courier driver for delivering the diagnostic samples.

### Study instruments

#### Questionnaires

During the first part of the study, participants answered a baseline questionnaire and a recurring questionnaire stored in the study app every 3 days until September 2020, corresponding to study time points 1–5, and only once for time points 6 and 7 in December 2020 and February 2021 [19].

For the second part of the study, access codes for an online follow-up questionnaire will be sent to all participants via mail during March 2022 (Supplementary Material Q1).

This questionnaire will include symptoms of infection and post-COVID-19 syndrome, activities of daily living (such as shopping or attending events), information on adherence to lockdown measures, and related precautions (social distancing, home office, personal protective measures, limited mobility), contact with children, and self-reported results of previous SARS-CoV-2 testing (since the onset of the pandemic) (Table 1).

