Limitations of the protocol can arise from its digital nature, as older individuals are less app-savvy or do not possess a smartphone. Participants were asked explicitly about problems answering the questionnaires during their first visit to the study center to mitigate these problems. A support hotline was set up to answer questions and was frequently used.

Initial study results have been published elsewhere and demonstrate vastly underestimated infection rates at the beginning of the pandemic [19]. The official trends of infection rates were well represented in our cohort. However, the absolute numbers were higher due to unrecorded cases. A high retention rate of 75–98% supports the feasibility of large-scale, long-term surveillance studies [19].

For our follow-up examination, we expect the seroprevalence to be remarkably higher than the preceding time points due to the more contagious variant B.1.1.529 (Omicron) and vastly increased infection rates worldwide, including our study area. With a current 7-day incidence rate of more than 1000 infections per 100,000 inhabitants in the municipal area of Luebeck, more than 1% of the overall population is being newly infected with SARS-CoV-2 every week. It needs to be emphasized that, although most cases in vaccinated patients have a mild disease course, there are still approximately 19% unvaccinated inhabitants above the age of four years in Germany at higher risk of severe courses [25]. In other developed countries like the USA or emerging countries, the rates of incompletely vaccinated people are even lower due to a lack of willingness or resources. Only 54% of the population worldwide have been vaccinated [26], which may even be an overestimate. Furthermore, high infection rates with SARS-CoV-2 are likely to aggravate long-term effects of the pandemic, particularly the prevalence of long- or post-COVID-19-syndrome. Although long-term effects occur more frequently in severe cases, up to 2.3% of mild COVID-19 cases show symptoms of post-COVID-19-syndrome more than 12 weeks after infection [27], highlighting the relevance of effective surveillance strategies even in a largely vaccinated population.

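### The only scheduled follow-up questionnaire, mailed in March 2022, comes too early to measure post-COVID syndrome after most Omicron-wave infections

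*Protocol article*

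**What the plan says.** Under Questionnaires, the article says that "access codes for an online follow-up questionnaire will be sent to all participants via mail during March 2022". The text below Fig. 1 describes one follow-up round: "participants will be invited via mail or email for follow-up testing on time point 8". No later round is scheduled. The Abstract and the Discussion say only that further examinations could be added ad hoc.

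The Background says the follow-up "will investigate the cohort after the sharp increase of cases in March 2022 due to the new SARS-CoV-2 B.1.1.529 (Omicron) variant". It gives two key topics: immunity after vaccination or infection, and post-COVID symptoms in the cohort. The Abstract and the end of the Discussion go further. They say the follow-up will allow study of the effects of the steep rise in infections on seroprevalence, post-COVID symptoms and risk factors.

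On the course of the wave, the Background dates the emergence of the variant ("especially variant B.1.1.529 (Omicron) in November 2021") and says that locally "the 7-day incidence rate rose from 20 infections per 100,000 inhabitants in October 2021 to 1190 infections per 100,000 inhabitants in February 2022". The Discussion treats the wave as still running, with more than 1% of the population newly infected each week.

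The only lag given for post-COVID syndrome is in the Discussion: "up to 2.3% of mild COVID-19 cases show symptoms of post-COVID-19-syndrome more than 12 weeks after infection".

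**The concern.** The survey goes out while the exposure it is meant to follow up is still happening. A participant infected in February 2022 who answers in March can report acute or lingering symptoms. That participant cannot yet show whether symptoms last beyond 12 weeks.

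At stake is the statement about the effect of the Omicron increase on post-COVID symptoms. The analysis can leave recent infections out, but few wave infections then remain. If it keeps them, the result depends on how they are handled: counting their current symptoms as post-COVID pushes the prevalence up, and keeping them in the denominator as unaffected pushes it down. The article does not say which would be done. No analysis can supply follow-up time that was not observed, so this is a matter of data collection and not a detail to be left to an analysis plan.

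**Working it through.** **The article's own figure.** 1000/100,000 = 1.00% per week, and 1190/100,000 = 1.19% per week. The Discussion's statement of more than 1% per week is reproduced.

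**Step 1: cut-off dates.** Latest infection date with 12 weeks of follow-up = reply date − 84 days.

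- 1 March 2022 − 84 days = 7 December 2021
- 15 March 2022 − 84 days = 21 December 2021
- 31 March 2022 − 84 days = 6 January 2022

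**Step 2: share of infections old enough.** Inputs from the Background are a 7-day incidence of 20 per 100,000 in October 2021 and 1190 in February 2022. Daily infections = 7-day incidence / 7. Share = infections from the start of counting to the cut-off, divided by infections from the start of counting to the reply date.

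The article does not give the path between the two points, so these assumptions were varied:

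- rise exponential or linear;
- rise starting between 1 and 31 October, with 20 per 100,000 before that;
- 1190 reached between 1 and 28 February, then flat.

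Counting starts on 1 October, or on 15 November as a stand-in for the start of Omicron.

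| Reply date | Rise | Since 1 October | Since 15 November |
|---|---|---|---|
| 1 March | exponential | 4.1–8.7% | 2.5–5.0% |
| 1 March | linear | 11.0–21.3% | 8.6–13.0% |
| 15 March | exponential | 5.8–9.8% | 4.4–7.6% |
| 15 March | linear | 15.9–26.6% | 14.1–20.0% |
| 31 March | exponential | 8.1–14.1% | 6.8–12.4% |
| 31 March | linear | 21.8–32.7% | 20.5–27.6% |

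*Most favourable case, written out:* linear rise from 1 October to 1 February (123 days), reply on 31 March.

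- To 6 January (98 days): (98 × 20 + (1170/123) × 4753)/7 = 6739 per 100,000, where 4753 = 0 + 1 + … + 97.
- To 31 March: (124 × 20 + (1170/123) × 7626 + 58 × 1190)/7 = 20,577 per 100,000, where 7626 = 0 + 1 + … + 123.
- Share: 6739/20,577 = 32.7%.

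*Least favourable case:* exponential rise from 31 October to 1 February, reply on 1 March. This gives 360/8737 = 4.1% since 1 October.

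**Step 3: late replies.** No closing date is given. If replies were accepted until 30 April, the cut-off would move to 5 February 2022, and 14–41% of infections since mid-November would qualify. That is still a minority.

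**Step 4: scale in the cohort.** At recorded incidence, and if all 3000 replied, there would be about 153–573 infections from mid-November to the reply date, of which about 5–158 would be at least 12 weeks old. At 2.3% that is 5 × 0.023 = 0.1 to 158 × 0.023 = 3.6 cases. Unrecorded infections would raise these counts. They would leave the shares unchanged if under-recording was constant over time.

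**Step 5: when the wave matures.** 28 February + 84 days = 23 May 2022. 31 March + 84 days = 23 June 2022.

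**The case against.** A reader might infer that the follow-up cannot answer its key question at all. The documents do not support that, for three reasons:

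- The key focus has two parts, and immunity does not depend on the 12 weeks.
- The post-COVID part is stated for the cohort as a whole, and the risk-factor aim under Study aims is not tied to Omicron.
- The questionnaire asks for test results since the pandemic began, so infections from 2020 until about December 2021 can be assessed in March 2022.

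These points stand, and they confine the problem to one sub-aim.

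It is also fair to say that the 12 weeks come from a cited rate in the Discussion and are not an adopted case definition. The full protocol or the questionnaire supplement may define the outcome differently. But this is the only lag the article offers, and it is part of the article's own case for studying post-COVID syndrome.

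A further objection is that how recent infections are handled belongs in an analysis plan that is not shown. That is right: no bias in a particular direction can be claimed. It does not meet the point about timing, because restricting the analysis leaves most wave infections without a 12-week outcome.

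Finally, further examinations are described as easy to add. This shows that a remedy is feasible, but none is scheduled.

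**Conclusion.** The point holds for one stated sub-aim: the effect of the Omicron-period increase on post-COVID symptoms. On the article's own dates, only about 4–33% of infections since October 2021, or 2.5–28% of those since mid-November, are at least 12 weeks old when the March questionnaire is answered. In every scenario tried, at least two thirds are too recent.

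The range rests on an assumed incidence path between the two published points, a flat level afterwards, replies within March, and the 12-week lag taken from the Discussion. Counting every infection from 15 November as Omicron is generous: if the variant took hold locally later than that, the share falls.

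This should be fixed, but it does not undermine the follow-up as a whole.

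**What to change.** Send the online symptom module once more, after the wave infections have matured: not before 23 May 2022 to cover infections up to 28 February, or 23 June 2022 to cover those up to 31 March. In both rounds, count post-COVID symptoms only for infections dated at least 12 weeks before the participant completed the questionnaire.

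If no repeat is possible, limit the post-COVID results to infections at least 12 weeks old at the March questionnaire. In the Abstract and Discussion, withdraw the claim that the follow-up will show the effect of the Omicron increase on post-COVID symptoms.

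The cost is one extra online mailing, some additional non-response and a later post-COVID result. No test-center visit is needed, and the immunity part is unaffected.
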